## Abstract

**Introduction:**

EHealth can help health service users take a more active role in decision-making and help health professionals guide the patient in this process. A digital tool has been designed to support maternal education (ME), and it is organised into four areas: (1) information, (2) communication, (3) health self-management and (4) clinical data. The main objective of the study is to evaluate the effectiveness of the EMAeHealth digital tool, and assess its usability and acceptability under routine conditions.

**Methods and analysis:**

Hybrid implementation-effectiveness design: (1) A cluster randomised, prospective, longitudinal, multicentre clinical trial to evaluate the effectiveness of EMAeHealth in (A) improving health-related quality of life (primary outcome), (B) improving self-efficacy for labour and childbirth and self-efficacy in breast feeding and (C) reducing the number of visits to the obstetric emergency services and health centre in situations of ‘non-pathological pregnancy’, ‘false labour pains’ and ‘non-pathological puerperium’. The EMAeHealth intervention plus usual care will be compared with receiving only usual care, which includes traditional ME. N=1080 participants, 540 for each study arm. Two measurements will be made throughout the pregnancy and three in the first 16 weeks post partum. (2) A mixed-method study to evaluate the usability and acceptability of the tool, barriers and facilitators for its use, and implementation in our health system: focus groups (women, professionals and agents involved) and a quantitative analysis of implementation indicators. Analysis: It will be carried out by intention to treat, using mixed models taking into account the hierarchical structure of the data and per protocol to evaluate the effectiveness of the express use of the digital tool.

**Ethics and dissemination:**

Clinical Research Ethics Committee of Euskadi, Spain, (Ref: PI2020044) approved this study. The results will be actively disseminated through manuscript publications and conference presentations.

**Trial registration number:**

NCT04937049.

Strengths and limitations of this studyEMAeHealth is the prototype of a digital tool that supports decision-making during the pregnancy and post partum. One strength is that it has been designed through Collaborative Action Research and is intended to be a complement to Maternal Education.A hybrid efficacy-implementation design will allow the effectiveness of EMAeHealth to be evaluated while collecting data on the implementation of the tool in ‘real-world’ conditions.Both patients and professionals have participated in the previous Collaborative Action Research and will be involved in the evaluation of the tool and in its implementation.One of the main strengths of the efficacy-implementation study is that it will result in an effective tool that will be perfectly adapted to the needs of the target population.A weakness is that it is possible the results cannot be directly extrapolated to a different context and it would be necessary to adapt the tool to the context where it will be implemented.

## Introduction

### Need to adapt maternal education to the current context

Antenatal education classes, including ’childbirth education programmes’, ’prenatal classes’ and antenatal groups, are attended by a large percentage of pregnant women worldwide.^1–3^ Both the high attendance of maternal education (ME) classes, and the fact that they take place at a time of transition, when readiness for change is higher, suggest that ME can be a valuable window of opportunity.^1 2^ However, the benefits of these programmes for participants and their newborn infants remain unclear, and classes are not normally based on the expressed needs of attendees, but rather on the messages that the educators themselves believe they should impart.^1^ It may be that studies aimed at evaluating the effectiveness of ME have tended to have methodological weaknesses, such as small sample sizes, lack of control for variables that could affect the delivery process and consideration of only part of the delivery process.^1^ Whatever the case, it has also been found in our setting that ME classes have not been associated with an improvement in most birth variables, whether physical or psychological, and have even increased birth anxiety in foreign women^3^; in this study, it was concluded that a new approach to these classes would be necessary. Other authors have come to the same conclusion, in light of their results.^4 5^ There is therefore a need to reorient ME by focusing on women’s needs and to evaluate the effectiveness of any initiatives to improve ME.

In order to establish a feasible and effective perinatal education programme, tailored to our setting, the team—following guidance published by the UK Medical Research Council for the development and evaluation of complex interventions in primary care—undertook: (A) a qualitative study with 30 women, exploring their needs during pregnancy and post partum; (B) two literature reviews on women’s needs at these times and theoretical models of health education and (3) seven discussion and consensus sessions with an expert panel of midwives, gynaecologists, paediatricians, paediatric and postpartum nurses.^6 7^ The aim was to involve women and professionals in the process of designing the new ME. Subsequently, a study was conducted to establish priorities with respect to ME using the Delphi technique and the nominal group approach. The objective of this study was to identify and prioritise the most important issues in ME in order to set goals and evaluate their achievement, that is, to ‘make ME evaluable’.^8^

The needs expressed by women in our population changed throughout pregnancy: initially they needed information to know that ‘everything was going well’; next, they needed more emotional support, to feel confident and self-reliant in dealing with their fears about childbirth and childcare; and finally, they needed more postpartum support and less pressure regarding breast feeding. They also preferred a comprehensive perinatal education programme—covering pregnancy, post partum, breast feeding and parenting—rather than just prenatal; and one that was more participatory and flexible and allowed for greater partner involvement. These were the results of the study with focus groups of women.^6^

Accordingly, ME was redefined as a complex intervention, which should extend from the beginning of pregnancy to the end of the puerperium, focusing on the needs of women and with the involvement of multiple health professionals. It would be an intervention whose general objective should be to enable women to make appropriate decisions to: (1) improve their health level and that of their family, (2) choose and responsibly face their birth and parenting model, and (3) maintain family and social support networks. The new model of ME includes multiple interventions capable of responding to the health needs of each woman at different moments of the childbearing process.^7 8^

### Design and relevance of an eHealth tool to support ME: EMAeHealth

EHealth interventions are becoming increasingly important and frequent.^9^ EHealth can help the health service user to take a more active role in decision-making and enable the health professional to guide the patient in this process.^10^ It can also contribute, at organisational level, to a more patient-centred model of healthcare.^11^

In addition, young women from all social strata consistently use the Internet as a source of information about their health.^12–15^ The information available on the websites they consult is positively correlated with the decisions they make about their health during the pregnancy and post partum.^12 16^ Pregnant and postpartum women use the internet because it offers immediate, detailed, entertaining, personalised or practical information.^13 17^

However, the lack of participation of health professionals in integrating healthcare and new technologies is felt,^12 18^ since the currently available range of information is not always reliable^19^ or contextualised.^20^ As the origin of a website has a direct effect on reliability, the participation of health professionals in the use, advice and generation of new technologies is essential.^15 21^

This team has designed a prototype digital tool called EMAeHealth involving healthcare professionals and patients, using a collaborative research process.^21^ The website, adapted to our context of implementation, is organised into four areas: (1) an information area, which is open to the public, provides information based on evidence and is permanently updated by healthcare professionals; (2) a communication area, which allows women to contact others in a similar situation, through forums or conversations, or consult their own midwife (3) a health self-management area, which has valid and reliable self-assessment instruments for checking or reflecting on their own health needs, and decision support tools such as the detection of the onset of labour or the detection of warning signs and symptoms in the post partum; and (4) a clinical data area, which allows women to keep their clinical data, to add the most recent, and share data with other professionals if they wish, under secure conditions. The tool is conceived as a complement that can reinforce ME; with resources that facilitate its accessibility, immediacy and continuity, as well as improving its results. Its incorporation into the Osakidetza-Basque Health Service corporate website will encourage its adoption by patients and professionals, as well as its safe use. The usual phases for the development of a digital tool are analysis, development, testing and production. The prototype is the result of the analysis, a proposal of the architecture and technical requirements that the digital tool must have in order to respond to the users’ needs. This is followed by development—or programming—and testing, which are carried out almost simultaneously, to detect and solve errors. Once the tool is ready, it is deployed in a production environment, making it available to all users of the system, in our case the Osakidetza-Basque Health Service corporate website.

### Study of the effectiveness of the tool while we are collecting useful information for its implementation in routine conditions

The evaluation of the effectiveness of digital tools aimed at health education during pregnancy is scarce and has had controversial results:^22 23^ the quality, reliability and effectiveness of current pregnancy apps is yet to be determined,^15 22 23^ and consequently, such studies to evaluate effectiveness are absolutely essential, especially if the digital tool comes from the healthcare system. In addition, there are barriers and facilitators that modify both the use of digital technology and its effectiveness in healthcare, where further study is needed.^13 16 17 24–26^ Fortunately, there are hybrid designs that enable testing of the clinical intervention and, at the same time, during the trial, gathering information on its application and/or its potential for application in real-world conditions.^27^ There are also frameworks, such as the RE-AIM (Reach, Effectiveness, Adoption, Implementation, Maintenance) Planning and Evaluation Framework, and Consolidated Framework for Implementation Research (CFIR), which can help in the task of studying the degree of adoption of an innovation, and guide in the data collection, analysis and interpretation of barriers and facilitators to implementation.^28 29^ Therefore, we conducted this study to find out if complementing traditional perinatal care with a tool—designed through a collaborative action-research process—translates into better health outcomes for women than those obtained with traditional care alone. In addition, we want to know if this type of tool is useful and acceptable to its users in real-life conditions.

## Objectives

The main objective of the study is twofold: on the one hand to evaluate the effectiveness of the EMAeHealth digital tool and its components (Information Area, Communication Area, Health Self-Management Area and Clinical Data Area), and on the other to assess the usability and acceptability of the tool under routine conditions.

The following are proposed as specific objectives:

To develop, test and deploy the EMAeHealth tool,^21^ with the structure described above, capable of offering information, responses via algorithm, links to available resources, secure data archiving and monitoring, connection between various systems and the possibility of data analysis establishing continuous feedback and readjustment of the information presented. To provide it with content related to pregnancy, childbirth and post partum.To evaluate the effectiveness of the tool in (1) improving health-related quality of life, (2) improving self-efficacy for labour and childbirth and self-efficacy in breast feeding and (3) reducing the number of visits to the obstetric emergency services and health centre in situations of ‘non-pathological pregnancy’, ‘false labour pains’ and ‘non-pathological puerperium’.To evaluate the usability and acceptability of the tool by women and professionals, and any barriers to its implementation.To estimate the differential impact that EMAeHealth could have, based on sociodemographic and/or population characteristics.

## Methods and analysis

This is an Effectiveness-implementation hybrid design type I,^26^ which combines (1) a multicentre, longitudinal, prospective, cluster randomised clinical trial to evaluate the effectiveness of EMAeHealth and (2) a mixed-method study to evaluate the usability and acceptability of the tool, barriers and facilitators for its use and implementation in our health system. The mixed-method study is made up of a qualitative study by focus groups (women, professionals and agents involved) and a quantitative analysis of implementation indicators (figure 1).

**Figure 1 F1:**
[figure not shown]
EMAeHealth design description. ME, maternal education; SF-36, Short Form 36.

For the effectiveness study, we have chosen a cluster randomised design to avoid, among other issues, contamination bias among women from the same centre, since they are likely to coincide, for example, in ME classes. In addition, as the intervention has been designed for shared decision-making, it did not seem appropriate for the same midwife to have women belonging to both control and intervention.

The study is being conducted between 2021 and 2023, with the first year dedicated to the development of the EMAeHealth digital tool. The general structure of the tool is described in the introduction. In the development of the prototype, the International Patient Decision Aid Standards were applied, using a collaborative action research process, involving experts and patients, with qualitative research techniques, as well as focus groups, prioritisation and consensus techniques.^21^ At this time, we are finalising content editing and software development and testing. We expect to start recruitment in July 2022. The participants will be followed up for a year, the period of time that the intervention lasts. The final months of 2023—first months of 2024 will be dedicated to the analysis and diffusion of results.

Regarding the study population, all Osakidetza-Basque Health Service public primary care centres that have midwives who are interested in optimising their clinical practice by adopting innovations will be eligible. In order to consider the centre eligible, the requirement will be that at least 50% of the midwives belonging to the centre have signed a collaboration agreement, as well as the approval of the Head of the Primary Care Centre.

Osakidetza-Basque Health System is the public healthcare system of the Basque Country, a region located in the north of Spain. Osakidetza was created by the Health Department of the Basque Government in 1983. All the public hospitals and primary care centres of the Basque Region are under this organisation, structured into several Integrated Health Organisations (IHO) spread throughout the Basque country. More than 30 000 professionals work for Osakidetza, and it could be considered the largest organisation in the Basque Country.

For the study of clinical effectiveness, an active surveillance system will be established to identify eligible patients, who are Spanish-speaking pregnant women attending their first appointment with the midwife between week 6 and 10 of gestation. Regarding their clinical profile, they are low-risk pregnant women. The midwives participating in the study will be in charge of recruiting them consecutively until they have the necessary sample from among the people using and not using the EMAeHealth tool (figure 2).

**Figure 2 F2:**
[figure not shown]
EMAeHealth effectiveness flow chart. ME, maternal education; SF-36, Short Form 36.

Regarding the mixed-method study, to evaluate the quantitative implementation indicators, all pregnant women who have seen their midwives at the start of gestation at the health centres will be included for 1 year after the implementation of EMAeHealth. The same goes for the qualitative evaluation, through focus groups of women and professionals from the health centres (model consent form as an online supplemental file 1).

10.1136/bmjopen-2021-055031.supp1Supplementary data

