### Outcomes

Access to EMAeHealth by women and professionals during the study period will be through access codes, which will allow the research team to track the use made by users of the tool while ensuring the confidentiality of the data. It also makes it possible, under safe conditions, to link this use with clinical variables from medical records and with the record of the forms filled in electronically at each measurement.

Results of clinical effectiveness: The primary outcome is change in Health-related quality of life (QoL), measured with the Spanish version of the Short Form 36 (SF-36) questionnaire.^30^ The secondary variables are the number and reasons for visits to the obstetric emergency service and to the health centre for non-pathological pregnancy situations, and the labour stage at the time of going to the hospital for suspected labour onset (measurement is carried out using the Bishop test/dilation in cm, effacement and breaking of waters (YES/NO)). As indirect indicators of autonomy in managing their own health and well-being, self-efficacy for labour and childbirth and self-efficacy in breast feeding will be measured using the Spanish version of Lowe’s CBSEI scales^31^ and the Breastfeeding Self-Efficacy Scale—SF,^32^ respectively.

Measurements of these variables will be performed at weeks 8 and 37 of pregnancy, and at weeks 1, 6 and 16 post partum. Contact with the woman and the response to the questionnaires will be carried out electronically (via mobile phone).

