Indicators of the implementation process: Qualitative indicators: Usability and acceptability of the tool by patients and professionals, as well as barriers and facilitators for its use and adoption in the health system. The qualitative evaluation will be carried out through focus groups of women and professionals, between 6 and 8 per group and as many as necessary until the discourse is saturated.^35^ A semistructured script will be developed for the sessions, based on the theoretical constructs of the CFIR,^28^ which will also serve as the basis for the analysis. The CFIR includes 37 constructs within 5 main domains: intervention characteristics, outer setting, inner setting, individual characteristics and implementation process. Overall, the CFIR aims to help identify potential factors (ie, barriers and facilitators) that are believed to influence implementation. Sessions will be audiorecorded and moderated by an expert in qualitative techniques while an assistant will take notes. Later the sessions will be transcribed and analysed. Quantitative indicators: adoption and frequency of the use of EMAeHealth and its areas according to stratification profiles and correlates with other variables (indicators: patients exposed to the digital tool, by centre and group; women with access to EMAeHealth who access the tool once; frequency of use of the tool, frequency of use of the different functions of the tool, etc).

Predictive, modifying and confounding variables: Patients: Age, parity, nationality, race, social class, educational level, marital status, work situation, distance to hospital, spontaneous pregnancy versus assisted reproductive technique, obstetric history and other clinical characteristics. Professionals: Sex, age, length of time in the position, type of contract, profile of adoption of innovations by professionals, measured by means of a questionnaire by Borracci *et al*, 2013.^36^ Health centres: reference IHOs, number of midwives and participation rate, rural or urban environment, and population served (figure 3).

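### Women enter the implementation indicators over a full year, but the stated calendar ends before later entrants complete the post-partum period, so use of post-partum functions would be understated relative to pregnancy functions

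*Protocol article*

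**What the plan says.** The protocol article defines the cohort for the quantitative implementation indicators under Methods and analysis, in the text after Figure 2: "all pregnant women who have seen their midwives at the start of gestation at the health centres will be included for 1 year after the" launch of the tool. No date is given on which recording of tool use stops.

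The other relevant statements are these:

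- **Calendar** (Methods and analysis, text after Figure 1). The study is placed in 2021 to 2023. "We expect to start recruitment in July 2022". "The final months of 2023—first months of 2024 will be dedicated to the analysis and diffusion of results".
- **Time per woman** (same place). "The participants will be followed up for a year, the period of time that the intervention lasts". Eligible women are those attending their "first appointment with the midwife between week 6 and 10 of gestation". Under Outcomes, measurements are set at "weeks 8 and 37 of pregnancy, and at weeks 1, 6 and 16 post partum".
- **Indicators** (Outcomes). The list includes "frequency of use of the tool, frequency of use of the different functions of the tool". Use is tracked through access codes during the study period and can be linked to clinical variables from the medical records.
- **Analysis** (Statistical methods). The indicators are summarised by central tendency, dispersion and proportions with 95% CIs, and related to predictors in mixed models. Observation time is not mentioned.

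**The concern.** Entry is staggered over a year, and each woman's pathway through the tool takes nearly another year. The two together do not fit between July 2022 and the end of 2023. A woman who enters late in the inclusion year reaches the post-partum stage late or not at all before the study period closes.

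Some functions can be used only after birth. The Introduction names decision support for warning signs in the post partum. If its uptake is a mean count or a proportion over all included women, those not yet delivered enter the denominator without any chance to use it. Pregnancy functions do not have this handicap to any comparable degree. A comparison across functions would then partly reflect how many women reached each stage, and a post-partum function could be judged little used for that reason alone. These indicators feed the implementation half of the study's twofold main objective.

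**Working it through.** The article gives no figure for observed exposure in the implementation cohort, so there is none to reproduce. Its one calculated figure, the trial size, is not in question here.

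**Inputs from the article.** Entry lasts 52 weeks. First midwife visit is at gestational weeks 6 to 10, with 8 as base case. The last measurement is 16 weeks post partum. Recruitment starts July 2022. The study period ends with 2023.

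**Assumptions.** Entry is even over the 52 weeks, birth is at gestational week 40, and roll-out coincides with the start of recruitment. The entry weeks and follow-up are stated for the effectiveness participants and are carried over to the wider cohort.

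**Step 1: does the calendar fit?** Time per woman is (40 − 8) + 16 = 48 weeks. The last entrant finishes at 52 + 48 = 100 weeks after the start, about the end of May or early June 2024. July 2022 to the end of 2023 is about 78 weeks. The gap is 100 − 78 = 22 weeks.

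**Step 2: who is cut short?** A woman entering at week e (0 to 52) gives birth at e + 32 and completes at e + 48. If capture closes at week T:

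- no post-partum time: e > T − 32
- full 16 weeks: e ≤ T − 48
- otherwise, T − 32 − e weeks are observed.

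For T = 78:

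- none: (52 − 46)/52 = 6/52 = 11.5%
- full: 30/52 = 57.7%
- less than full, including none: 22/52 = 42.3%
- mean post-partum weeks: (30 × 16 + 16 × 8)/52 = 608/52 = 11.69, and 11.69/16 = 73%
- mean pregnancy weeks lost: 6 × 3/52 = 0.35 of 32, so 99% of pregnancy time is observed.

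With entry at week 6 or week 10 instead of 8, the 73% becomes 69% or 77%, and the 11.5% becomes 15% or 8%.

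**Step 3: vary the closing date.**

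| Log capture closes | No post-partum time | Full 16 weeks | Post-partum time observed |
|---|---|---|---|
| 52 weeks (with the inclusion year) | 62% | 8% | 23% |
| 65 weeks (about end September 2023) | 37% | 33% | 48% |
| 78 weeks (end 2023) | 12% | 58% | 73% |
| 91 weeks (about March 2024) | 0% | 83% | 95% |
| 100 weeks (every woman completed) | 0% | 100% | 100% |

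**Step 4: what this does to the indicators.** If post-partum use is constant over the 16 weeks, a cumulative count at T = 78 captures 73% of it, against 99% for pregnancy functions. For an ever-used proportion, a first use that falls w weeks after birth is captured with probability (46 − w)/52. That is 88% for use straight after birth and 58% for use at week 16.

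**The case against.** The strongest reply is that the article gives an inclusion period and no closing date for the logs. If each woman is observed for her own year, nothing is cut off. If capture runs to about March 2024, only about 5% of post-partum time is lost. The recruitment date is an expectation, and the caption to the timetable figure calls a period approximate and dependent on the tool's availability. Denominators and time-at-risk offsets are also ordinary content for an analysis plan that is not shown.

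Much of this limits the size of the problem. It does not remove it. The inclusion year is tied to roll-out, which fits poorly with a separate year for each woman. Complete observation of a year of entrants needs capture to run to about June 2024, beyond both the study period and the months given to analysis. That is a mismatch between stated dates, not a detail left to another document.

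A reader might infer three stronger things that the article does not support:

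- **Logs stop at 52 weeks, losing 77% of post-partum time.** Nothing says so. Tracking is tied to the study period, which points to a later close.
- **Women are cut off on every reading.** They are not if each woman is followed for her own full year.
- **Relations between use and predictors are confounded by entry date.** That needs predictors associated with entry date, and none is shown. Without such a link, unequal exposure mainly adds noise.

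It is also fair that usability and acceptability are listed as qualitative indicators, assessed in focus groups. The usage counts contribute to that half of the objective but do not settle it alone.

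**Conclusion.** The point stands in a conditional form. On the article's own dates, a year of entry followed by about 48 weeks per woman does not fit before the study period ends, so part of the cohort has no post-partum observation or an incomplete one. With even entry and capture to the end of 2023, 12% have none, 42% have less than the full period, and 73% of intended post-partum time is seen. The shortfall grows if logs close before the end of 2023, as they may with analysis starting in that year's final months. It shrinks to about 5% with capture to about March 2024.

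The effect is confined to cumulative use and ever-used proportions for post-partum functions calculated over all included women. The count of women exposed to the tool is unaffected, and the proportion who access it once is barely affected. The randomised comparison and the primary outcome are untouched.

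**What to change.** 1. Where the implementation cohort is defined, state when entry ends and when log capture ends, and make both consistent with the study calendar.
2. Report use per woman-week at risk, separately for pregnancy and post partum. For counts, this means the log of time at risk as an offset in the mixed models already planned.
3. Give ever-used proportions for post-partum functions only among women whose post-partum period lies within the log window, and state that denominator.

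The cost is mainly wording. The Outcomes section says use can already be linked to medical records, from which entry and birth dates should be available. The downside is fewer women in the post-partum denominators: with capture to the end of 2023, about 58% have the full 16 weeks. The rate in item 2 assumes fairly steady use within each stage, and repeating it in the fully observed women would check that.
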